# 3. STUDY DESIGN

The study is double-blind placebo-controlled randomized with the patient him/herself as an internal control. To get enough power we aim to include 20 (see power analysis) adults ≥18 years with Birt-Hogg-Dubé syndrome. Inclusion will take place in two hospitals in the Netherlands; Maastricht University Medical Centre and VU Medical Centre Amsterdam. After inclusion patients are treated with rapamycin in one facial half and a placebo in the other. Patient and physician are blinded until the end of the study. The solution (placebo and verum) is applied according to standardized instructions. The study will proceed according to standardized trial monitor forms (Annex F4). These forms describe how the patient is to be examined at each visit. The skin will be evaluated by 3 observers; the investigator and two dermatologists. They will assess a difference in fibrofolliculoma status on a 7-point rating scale ranging from -3 (strong worsening) to +3 (strong improvement). Although patients evaluate their skin on this scale too, we will not include their measurements in the analysis because of bias. For further explanation see chapter 7.

Patients will be followed-up at 3 months and at 6 months.

It is likely that, during the study, one facial half will improve because of treatment with rapamycin. However, we do not think it is ethical to ask our patients to deal with one improved facial half and one unimproved facial half. Moreover, when patients see a difference between facial sides, they might apply the solution, that they think is the effective one, on both facial sides. To prevent this situation we developed the following study design:

When a clear difference arises between facial sides, blinding will be broken and we will proceed with an open-label study. There are a few conditions to break the blinding, pointed out below.

- Two of three observers have to see a significant difference. This means that there must be an improvement (or worsening, which we don’t expect) of at least 2 points on the 7 point rating scale.
- When there is a significant difference, the blinding will be broken. Then it will also become clear whether the improved side is the rapamycin-treated side. In this case patients are allowed to use rapamycin on the entire face.
- When patients see a difference between the left and right facial side themselves, they can make an earlier appointment.

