- To prevent a large proportion of patients form dropping out at an early stage of the study, we aim to continue treatment for at least 3 months. When patients contact us before the end of this period, we will try to motivate them to continue treatment.
- It is also possible that patients see a moderate or strong improvement, while the observers just see a minimal one. Also in this case we will try to motivate patients to proceed with the study for one more month.

In the last two situations described above it will be difficult to convince patients to continue treatment before blinding is to be broken. We think that a good explanation of the importance of the trial and the benefits for the patient, will help to retain patient adherence. Of course we prefer to continue the study as long as possible. However, when a patient really wants to stop treatment due to a clear difference between facial halves, we will break the blinding.

Although we don’t expect it, rapamycin might worsen skin lesions in individual patients. In this situation, the trial will end, just for this specific patient. Another condition to terminate the study prematurely for a specific patient is when it turns out that rapamycin has no effect at all. In our opinion, rapamycin has no effect when no improvement has occurred after 3 months. We base this 3 month period on several clinical studies in which rapamycin was used for treatment of dermatological diseases. In these studies, the effect of rapamycin was visible within 3 months [12, 15-17].

See Annex F4 for a flow chart that gives an overview of the procedures that subjects undergo and a flow chart for patients. Procedures are also described in chapter 7.

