# *7.* METHODS

## 7.1 Study parameters/endpoints

### 7.1.1 Main study parameter/endpoint

The main study parameter is the change in lesion size and count (severity) as measured by the investigator, the patient and two independent dermatologists. For lesion size we use the average size of fibrofolliculomas in millimetres.

Severity is indicated on a 7-point scale:

-3= strong worsening

-2= moderate worsening

-1= minimal worsening

0= no improvement

1= minimal improvement

2= moderate improvement

3= strong improvement

Significant regression is defined as a difference in assessment by at least 2 of 3 observers, with at least +2 points. The observers are the investigator and two independent physicians. Assessment of size and count is made on the basis of medical photos of the face. These photos will be standardized; same distance, background, colour and light profile etc.

Confirmation by visual examination.

Professor [name], professor in clinical epidemiology of Maastricht UMC has advised us to use this 7-point scale. Given the fact that there are no previous randomized controlled trials in the BHD syndrome, there is no previously validated scale that we can use for this disease. That is why we have chosen for a 7-point Likert scale. It is known that the Likert scale has good measurement properties and it is used often in trials in which skin changes have to be assessed [19, 20].

During the study we will determine the intra- and inter-observer variability by means of a weighted kappa test. Per patient 2 photographs will be assessed with the 7-point scale; at 3 months and at 6 months. These photographs will be compared with a baseline photo. To measure the inter- and intra observer variability we need at least 3 observers. These observers will be the researcher and two independent physicians. They will assess every photo twice. To prevent bias, the assessments must be at least 2 months apart. Besides evaluation based on photographs, the researcher as well as the patient can assess facial progress during the appointments. These assessments are not included in the analysis, only the results based on the photographs provided by the researcher, physician 1 and physician 2 will be used. This means there will be 6 scores for every patient per follow-up visit. Of these results, the most frequently given score will be used for the analysis.

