## 9.2 Primary analysis

During the trial patients apply rapamycin solution in one facial half and placebo solution in the other facial half. This means that the patient is his/her own control.

Primary output measure is change in facial fibrofolliculoma size and count (severity) as measured by the investigator, two independent physicians and the patient. The response to treatment will be assessed with a 7-point rating scale, ranging from -3 (strong worsening) to +3 (strong improvement). This scale is described in chapter 7. Significant regression is defined as assessment by at least 2 of 3 observers with at least +2 points. Rapamycin will be compared with placebo using a McNemar ‘s chi square test for paired samples. Both an intention to treat and a per protocol analysis will be performed.

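### Photo readings are scored as change from baseline with no masking of time order, so the absolute +2 response rates and the no-improvement call can depend on what readers expect

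*Protocol*

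**What the plan says.** Section 7.1.1 sets out the reading procedure. "Assessment of size and count is made on the basis of medical photos of the face", and of the two follow-up photographs it says: "These photographs will be compared with a baseline photo". The scale runs from -3 (strong worsening) to +3 (strong improvement). Three readers score each photo twice, at least two months apart, a gap the section justifies as a guard against bias: "This means there will be 6 scores for every patient per follow-up visit". The most frequent of these scores is analysed. The photos are standardised for distance, background, colour and light.

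Sections 3 and 7.2 blind patient and physician to which side receives rapamycin. No section describes masking of which image is earlier.

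The scores are used in three ways:

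- **Response**, Section 9.2: "Significant regression is defined as assessment by at least 2 of 3 observers with at least +2 points". Section 7.1.1 words the same rule as a difference in assessment.
- **No effect**, Section 3: "In our opinion, rapamycin has no effect when no improvement has occurred after 3 months". As worded, this is not a comparison with placebo.
- **Code break**, Section 3: "When a clear difference arises between facial sides, blinding will be broken". The condition is then "Two of three observers have to see a significant difference", explained as an improvement or worsening "of at least 2 points on the 7 point rating scale". Section 7.3 has the need for unblinding assessed at the 3-month visit.

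**The concern.** A reader can give a signed change only by knowing, or assuming, which image came first, unless the sign is added after a masked reading. Section 7.1.1 has no such step. A reader who expects change for the better may therefore score small or ambiguous differences upward, whichever side is being judged.

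The conditions for this are present. Section 3 considers improvement of one facial half likely. One reader is the investigator, who also examines the patients. Section 7.1.1 says that no validated scale exists for this disease. Section 3 already leaves out patients' own scores because of bias, so the protocol accepts that expectation can move this scale.

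What is at stake is each quantity that uses the score as an absolute value: the response rate reported for each half, the size of the difference between them once the +2 cut is applied, and the no-improvement judgement at 3 months.

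**Working it through.** **The plan's own figure.** Section 4.4 plans for a 35% difference in response, 90% power, two-sided 0.05 and 17 patients. With no placebo-only responders, the uncorrected McNemar chi-square rejects when at least 4 patients respond on rapamycin only, because 4²/4 = 4 exceeds 3.84 and 3²/3 = 3 does not. Power is P(Bin(17, 0.35) ≥ 4) = 0.897. With 15% drop-out, 17/0.85 = 20. The figure is not at issue here. It shows that the target effect is a difference between two rates, each obtained after the +2 cut.

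**Inputs for the size of the problem.** From the documents: the scale, three readers, +2 from at least two of three, 17 pairs. Assumed, because the documents give nothing: true change with SD 1, mean 1.0 on rapamycin and 0 on placebo, within-patient correlation 0.4, reader error SD 0.7, and an expectation shift δ common to both halves. The model scores each half separately and uses one reading per reader. It does not model the most-frequent-of-six rule.

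**Formula.** A rounded score is +2 or more when the underlying value is at least 1.5. For true change t, one reader calls +2 or more with probability p(t) = Φ((t + δ − 1.5)/0.7), and at least two of three do so with probability 3p² − 2p³. The response rate is the average of this over t ~ N(μ, 1). Hand check: at μ = 1.0 and δ = 0.5 the centre lies on the cut, so by symmetry the rate is 50%. For no improvement (score 0 or lower from at least two of three), replace p by Φ((0.5 − t − δ)/0.7).

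| Shift δ | Rapamycin response | Placebo response | Difference | No improvement, rapamycin half |
|---|---|---|---|---|
| 0 | 33% | 9% | 24 points | 33% |
| 0.25 | 41% | 13% | 28 points | 25% |
| 0.5 | 50% | 18% | 32 points | 18% |
| 1.0 | 67-68% | 33% | 35 points | 9% |

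The shift is the same on both halves and the drug effect is fixed, yet the difference moves from 24 to 35 points. A common shift does not cancel after a threshold. In this model the difference peaks when the cut lies midway between the two means (0.5 + δ = 1.5, so δ = 1.0) and would shrink beyond that. The direction is therefore not general.

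**The paired test under no effect.** If rapamycin does nothing and sides are masked, the two halves are exchangeable with or without δ, so rapamycin-only and placebo-only responders stay equally likely. A second assumed model (SD 1.0 between patients, 0.7 between halves, 0.7 between readers; 17 patients, 40,000 simulated trials) gives, for shifts of 0 / 0.5 / 1.0:

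- response per half: 12.5% / 22% / 35%
- no improvement on the rapamycin half: 65% / 50% / 35%
- uncorrected McNemar rejection: 2.4% / 4.1% / 5.1%

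Rejection approaches the nominal 5% because there are more discordant pairs, not because one side is favoured.

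**Code breaks.** In the same no-effect runs, an absolute +2 on either half occurs in 20% / 33% / 49% of patients. A 2-point difference between halves occurs in 22% / 22% / 20%. Only the absolute reading responds to the shift.

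**The case against.** The strongest reply is that the within-face placebo half, with side masked and a paired test, is the control for any expectation shared by both sides. That stands for the test under no effect. It does not rescue the rate reported for each half, the size of the difference when the drug works, or a no-improvement rule that makes no reference to placebo.

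A second reply is that the protocol is silent rather than wrong, and that the trial monitor forms in Annex F4 are not shown. A reader might infer that the baseline image is openly labelled, that whole faces are displayed, or that each half is judged with the other in view. None of this is written: Section 7.1.1 mentions only photos of the face and does not describe scoring by half. The silence still counts, because that section specifies the reading in detail, including a safeguard against bias in repeat readings, and asks for a signed change.

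Third, Section 3 expects improvement on one half, whereas the model shifts both. That is fair. The common shift is an assumption, based on readers not knowing which half is treated. Its size is also assumed, so the table shows sensitivity and is not an estimate.

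Finally, signed change against a baseline photo is a legitimate choice beside a concurrent masked control, and the investigator may recognise time order even in coded images. Both points limit the gain from a change without removing it.

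**Conclusion.** The concern holds in a limited form. With time order unmasked, expectation of improvement can raise the absolute +2 rate on both halves, alter the estimated response-rate difference when rapamycin works, and make no-improvement findings rarer. The size is unknown. Under the first assumed model, shifts of 0.25 to 1.0 point take the rapamycin rate from about 33% to 41-68%, the placebo rate from about 9% to 13-33%, and the difference from 24 to 28-35 points.

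Three stronger conclusions are tempting and are not supported:

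- **That the primary test is biased.** Under no effect it is not, as long as side masking holds.
- **That more patients would be stopped for lack of effect.** The direction is the opposite: an upward shift makes that call less frequent.
- **That code breaks multiply.** This follows only from the absolute 2-point wording in Section 3. Under the between-sides wording of Sections 3 and 7.2 a common shift does not raise them, and Section 7.3 places the decision at the visit rather than at the photo reading.

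**What to change.** In Section 7.1.1, for the photo readings used in the analysis:

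- Present the baseline and follow-up images of each facial half as a coded, cropped pair, in random order and with dates hidden.
- Have the reader state which image is better and by how much (0 to 3).
- Have the data manager attach the sign afterwards, before the response rule or the most-frequent-score rule is applied. This keeps the existing -3 to +3 scale.
- Use the same procedure for both readings.

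The cost is image preparation time and a changed scoring sheet, with no extra reader, visit or patient. Sensitivity to small changes may be slightly lower. Masking will be incomplete for the investigator as reader, who also sees the patients at visits.

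Masked photo reading does not reach decisions taken at the visit. The wordings of the code-break and no-effect rules in Sections 3, 7.2 and 7.3 should be reconciled separately.

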## 4.4 Sample size calculation

Sample size is calculated to detect a difference of 35% in response as measured with a 7-point scale with a power of 90% and a type 1 error, 2 sided, of 0.05. Using McNemar’s chi-square test for matched pairs (each patient serves as his/her own control) we would need 17 patients. Taking into account 15% drop-outs we need to include 20 patients.

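### Section 7.1.1 gives two rules for the primary response (2 of 3 observers at +2 or more, and the most frequent of six readings) that can disagree, and the response of each facial half is never defined

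*Protocol*

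**What the plan says.** **Response rule.** Protocol section 7.1.1: "Significant regression is defined as a difference in assessment by at least 2 of 3 observers, with at least +2 points". Section 9.2 repeats the definition but drops the word for a difference, so there it reads as a plain score of +2 or more.

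**Score analysed.** Section 7.1.1 has one photograph of the face per follow-up visit (3 and 6 months) compared with a baseline photograph. Three observers each read it twice, at least two months apart. It concludes: "This means there will be 6 scores for every patient per follow-up visit", and then: "Of these results, the most frequently given score will be used for the analysis". Nothing links this score to the 2-of-3 definition, and there is no rule for ties.

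**Test.** Sections 4.4 and 9.2 compare rapamycin with placebo by McNemar's test for matched pairs, the pair being the two halves of one face. Section 4.4 sets a "type 1 error, 2 sided, of 0.05" and concludes that "we would need 17 patients", or 20 after 15% drop-out.

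**Assessors.** Section 9.2: "Primary output measure is change in facial fibrofolliculoma size and count (severity) as measured by the investigator, two independent physicians and the patient". The opening of 7.1.1 also lists the patient. Section 3 says of patients' scores: "we will not include their measurements in the analysis because of bias". The end of 7.1.1 limits the analysis to photograph scores from the researcher and the two physicians.

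**The concern.** A primary endpoint should give one answer for one set of readings. Here the definition of response and the statement of which score is analysed are separate rules, and both are presented as the basis of the primary analysis. Whoever applies the protocol must choose between them, and could do so after seeing the data. In a trial this small, reclassifying one or two patients can change the conclusion.

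The second difficulty is the unit that is scored. The comparison is between the halves of one face, but scoring is described per patient and per photograph, against baseline. The wording in 7.1.1 and 9.2 also leaves open whether +2 is a difference between halves or a change from baseline on one half.

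**Working it through.** **1. The protocol's own count.** 3 observers × 2 readings × 1 photograph = 6 scores per patient per visit, as stated. Separate scores for each half would be 3 × 2 × 2 = 12. So the stated six fits one rating per photograph. That is an inference, because the text does not say the face is rated as a whole.

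**2. Do the two rules agree?** Each bracket holds one observer's first and second reading.

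| Readings | Most frequent score | 2 of 3 observers at +2 or more |
|---|---|---|
| (0,1), (3,1), (3,1) | 1 (three times): non-response | Yes on first readings, no on second |
| (1,1), (2,3), (2,3) | 1, 2 and 3 tie, twice each: undefined | Yes on either reading |
| (2,2), (1,0), (−1,−2) | 2 (twice): response | No, only one observer |

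The rules fail in both directions. The first row also shows that the 2-of-3 rule is itself incomplete when readings are taken twice, since it does not say which reading counts.

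Enumerating all 7⁶ = 117,649 possible score sets confirms this:
- In 3,840 sets, two or more observers first scored at least +2 while the mode, or every tied mode, is below +2.
- In 720 sets, the mode is at or above +2 although fewer than two observers reached +2 on either reading.
- In no set do two observers reach +2 on both readings while the mode lies wholly below +2. In 90 such sets the mode ties across the cut.

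These counts show what is possible, not how likely it is.

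**3. How often?** The protocol gives no observer variability, so this step rests on assumptions: true score SD 1; observer SD and reading SD equal, both 0.3 or both 0.5; scores rounded and limited to −3 to +3; 200,000 simulated sets for each case. A call is counted as in conflict if the mode ties across +2, or if it falls on the other side of +2 from the 2-of-3 rule on first readings.

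| SDs | Exact agreement of an observer's two readings (mean +1) | Tied mode (mean +1) | In conflict, mean +1 | In conflict, mean 0 |
|---|---|---|---|---|
| 0.3 / 0.3 | 67% | 14.7% | 7.2% | 2.8% |
| 0.5 / 0.5 | 51% | 19.2% | 12.3% | 5.6% |

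With 20 rapamycin halves at mean +1 and 20 placebo halves at mean 0:
- SDs 0.3: 20 × 0.072 + 20 × 0.028 = 1.44 + 0.56 = 2.0 of 40 calls.
- SDs 0.5: 20 × 0.123 + 20 × 0.056 = 2.46 + 1.12 = 3.6 of 40 calls.

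Most of these are ties. At mean +1, a unique mode contradicts the 2-of-3 rule in only 1.8% and 4.1% of calls.

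**4. How few patients decide the result?** With b patients responding only on the rapamycin half and c only on the placebo half, McNemar's statistic is (b − c)²/(b + c), compared with 3.84.
- Uncorrected: 3–0 gives 3.0 and 4–0 gives 4.0, so 4–0 suffices.
- Exact: 5–0 gives 2 × 0.5⁵ = 0.0625 and 6–0 gives 2 × 0.5⁶ = 0.031, so 6–0 is needed.

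The stated sample size leans on these thresholds. With 17 patients, a 35% chance of responding on the rapamycin half only and none on placebo only, the probability of at least four discordant patients is 89.7%. That matches the planned 90% for the uncorrected test.

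**The case against.** The strongest reply is that the intent is clear. The Summary places the endpoint in the treated area, section 3 speaks of differences between facial sides, and 9.2 compares rapamycin with placebo. Six scores per patient may be loose counting, and the forms in Annex F4, which are not at hand, may already score each side.

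Much of this stands. A reader might infer that the trial produces a single whole-face score, so that the treatment contrast cannot be formed. The documents do not support that. One score per patient is only inferred from 3 × 2 × 1. Even one signed between-side score per patient would give the discordant counts, since McNemar's statistic uses only b and c. What remains is that the half-face response is undefined, while the comparison with a baseline photograph sits poorly with the between-side reading.

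A reader might also infer that patients' own ratings enter the primary analysis. They do not. Section 3 and the end of 7.1.1 exclude them, and the responder definition in 9.2 has room for three observers only. The two sentences naming the patient are residual wording. Only section 3 gives bias as the reason for exclusion.

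A tie-break could be left to an analysis plan. The choice between two stated primary rules is different, because the protocol has already fixed both.

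Finally, a reader might infer that second readings are unblinded, since they come at least two months later and unblinding is considered at 3 months. No section says so.

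**Conclusion.** The point holds. Sections 7.1.1 and 9.2 state a response rule that the mode-of-six sentence in 7.1.1 can contradict or leave undefined. This needs no assumption, because the worked readings show it. The half-face response used in the paired comparison is also not defined, and the two wordings of the +2 criterion leave its reference open.

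The size is illustrative: about 2 to 4 of 40 half-face calls in conflict or tied across +2, under the assumed SDs of 0.3 to 0.5 and means of +1 and 0. It would rise with poorer observer agreement. Set against a threshold of 4 to 6 discordant patients, that is enough to matter. The correction should be made before any photographs are read or the code is opened for analysis. The patient wording is a minor inconsistency.

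**What to change.** Change 7.1.1 and 9.2 only:

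- Each observer scores each facial half separately against that half's own baseline photograph.
- A half is a responder if at least 2 of the 3 observers give +2 or more at their first reading.
- Second readings serve only the intra-observer kappa.
- Delete the sentence that takes the most frequent of six scores.
- State six scores per half, 12 per patient, at each visit.
- Name the one visit that is primary; otherwise the rule still gives two responses per half.
- Use the same wording of the definition in both sections.
- Minor: remove the patient from the primary-measure sentences in 7.1.1 and 9.2, to agree with section 3 and the end of 7.1.1.

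Leave the unblinding rule in section 3 as a separate rule. It covers change in either direction and serves another purpose, so it should not be folded into the responder definition.

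Other single rules could work, such as keeping the mode with a stated tie rule and an explicit link to the +2 cut. The 2-of-3 rule on first readings stays closest to the definition that both sections already give.

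The cost is protocol wording and two scores per photograph from each observer instead of one. No extra patients, visits or observers are needed, and the stated sample-size inputs do not change. The price is that second readings no longer contribute to the primary endpoint.
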